### Safety and monitoring

An independent data and safety monitoring board comprising cardiovascular surgeons, anesthesiologists and statisticians will oversee the progress and safety of the study, including adverse events and morbidity. All adverse events will be evaluated for severity. Any severe adverse events will be recorded on the CRF and reported within 24 h to the Board and the Biological and Medical Ethics Committee of West China Hospital.

All unexpected major cardiovascular, cerebrovascular, and other serious adverse events not listed in the protocol will be reported to the coordinating center within 24 h. The chief principal investigator will be responsible for all adverse event reporting. All adverse events will be closely followed until resolution or stabilization. A local investigator will review all reports of adverse events.

### Data management and quality control

All CRFs will be immediately entered into a secure, web-based system hosted by the Data Coordinating Center as soon as they are received. Designated research team members will be authorized to access the allocation system and electronic CRFs by entering the patient’s unique participant identification number, initials, and date of birth in an online form. If data are entered incompletely or incorrectly, the principal investigator will contact the participating centers for clarification.

To control the quality of this study, all perfusionists will receive centralized training before the trial begins. All stored records will be kept secure and confidential according to standard guidelines. A reason must be indicated whenever data are altered, and all alterations will be saved.

### Sample size calculation

The sample size was calculated based on the primary outcome of our unpublished pilot study (manuscript in preparation), carried out at West China Hospital (Biomedical Ethics Committee approval no. 201824). In this study, we included 76 patients (*n* = 38 in each group), and defined the primary outcome as the abovementioned 30-day composite of operative mortality and major complications. In this pilot study, 13 of 38 control patients (34.2%) suffered the following outcomes: death, 4; paraplegia, 1; postoperative renal failure, 7; severe liver dysfunction, 4; or gastrointestinal complications, 1. A total of 9 of 38 patients in the RIVP group (23.7%) experienced the following outcomes: death, 3; paraplegia, 0; postoperative renal failure, 6; severe liver dysfunction, 1; or gastrointestinal complications, 1. The trial is planned to have 80% test power with a two-sided type I error rate of 5%, assuming a dropout rate of 10% over the course of the entire study. For statistical significance, 636 patients (318 participants in each arm) will be required for this trial according to the following statistical formula not including the 76 patients in the pilot study:$$ \mathrm{n}=\frac{{\left({Z}_{1-\alpha /2}+{Z}_{1-\beta}\right)}^2\left[{p}_1\left(1-{p}_1\right)+{p}_2\left(1-{p}_2\right)\right]}{\delta^2} $$

### Data analysis

All patients will be analyzed according to the intention-to-treat protocol. Data analysis will be performed by a statistician using SPSS 20.0 (IBM, Chicago, IL, USA). Differences associated with *p* < 0.05 will be considered statistically significant. Continuous variables will be expressed as mean ± standard deviation or median (interquartile range), and differences in such variables will be analyzed using an independent *t* test or the Wilcoxon signed-rank test, depending on whether data are normally distributed. Categorical variables will be described as numbers (percentages), and differences in such variables will be analyzed using a *chi-square test* and *Fisher’s exact test*. *Kaplan-Meier* curves and *log-rank* analysis will be used to compare inter-group differences in primary and secondary outcomes. Univariate and multivariate logistic regression will be performed to determine relative risk of primary and secondary outcomes in the RIVP group compared with the control group.

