## Methods

### Study design

This study is designed as a multicenter, randomized controlled, assessor-blind, parallel-group study with a superiority framework. Five clinical research centers in China will participate: West China Hospital of Sichuan University, Second Affiliated Hospital of Nanjing Medical University, First Affiliated Hospital of Wannan Medical University, The Second Xiangya Hospital of Central South University, and First Affiliated Hospital of the University of South China.

A total of 636 participants with type A aortic dissection will be randomly assigned by computer to either the MHCA (control) group or the RIVP group at a ratio of 1:1. Patients assigned to the control group will receive selective ACP alone under moderate hypothermia, while patients in the RIVP group will receive selective ACP combined with RIVP under moderate hypothermia. All patients will be admitted to a cardiovascular ICU after surgery, where they will remain until they are considered stable enough to transfer back to a general unit. Postoperative follow-up will be conducted throughout hospitalization (regardless of length of stay) and for up to 30 days after surgery if the patient is discharged, which will be sufficient to show the prognosis of surgical treatment. Patient enrollment began in January 2019 and is expected to be complete within 3 years thereafter. The following members of the study will be blinded to the patients’ group allocation: patients themselves, outcome assessors, and the statistician.

Perfusionists and surgeons in the trial will be experienced in performing the necessary procedures. Interventions will be carried out intraoperatively. Patients’ medical records will be reviewed for in-hospital complications and medication usage.

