### Recruitment of study population

Recruitment began on 1 January 2019 and is expected to be complete within 36 months (31 December 2021). Participants present on surgical lists will be recruited from the emergency department (ED), the cardiovascular wards or cardiac ICU depending on the coordinating center. Patients transferred directly to the OR will be recruited in the ED. Patients transferred to the cardiac ICU or ward under sedation and blood pressure control will be recruited in the ICU. The surgery need not be postponed for obtaining consent, even if the patient is transferred directly to the OR. If a patient with AAAD in the ED requires emergency surgery, the surgical fellow will be informed and will inform the anesthesiologist, research assessors and perfusionist to obtain the relevant consents in the ED.

After surgical consent is obtained by surgical fellows, a researcher will clearly explain to patients or their relatives sufficient information about this trial, including the benefits and drawbacks associated with participation. Simple language will be used to facilitate the understanding of medical terms. Participants who give consent will provide demographic and general medical data as described below in the section “Baseline study visit.”

The target study population is all patients aged 18 years or older diagnosed with AAAD and scheduled for elective or emergency TARS under CPB. Patients are eligible for the study if they are older than 18 years old and show AAAD on contrast computed tomography. Patients will be excluded from the study if they are unable to understand or give informed consent, if they are pregnant or if they are already participating in another clinical trial that might interfere with the primary or secondary outcomes of the present trial. Patients will also be excluded if they have had a hemi-arch replacement or if they or their relatives revoke consent. Patients can leave the study at any time for any reason if they wish to do so without any consequences. Patients who withdraw from the study will not be replaced. Withdrawals will be documented in the electronic case report form (eCRF). The investigator can decide to withdraw a participant from the study for urgent medical reasons.

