### Baseline study visit

As part of the baseline visit, we will collect patient information including age, height, weight, European System for Cardiac Operative Risk Evaluation (EuroSCORE II) [35], smoking and drinking status, diabetes mellitus, peripheral arterial disease, lipid profile, pulmonary and cardio-cerebral co-morbidity, and pulmonary infection during the preceding 30 days. Preoperative hematology and biochemistry assessments will also be performed including full blood count, electrolytes, liver and renal function tests, coagulation profile, thyroid function tests, and C-reactive protein. Enhanced thoracic and abdominal computed tomography will be performed to confirm the preoperative diagnosis, and preoperative transthoracic echocardiography will be used to measure left ventricular function as well as to detect valvular disease or other pathologies that meet the exclusion criteria. Additional clinical and study data will also be collected at baseline, as well as at other study time points (Fig. 1).

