Secondary outcomes will include the proportion of patients with a stroke/cerebrovascular incident, paraparesis, postoperative prolonged intubation (> 48 h), temporary neurological deficit, myocardial infarction (MI), acute kidney injury not requiring dialysis, surgical re-exploration for bleeding, and deep sternal wound infection. Patients who require assistance to stand or to walk will be defined as having paraparesis (Tarlov score 3–4) [39]. Temporary neurological deficit [40] will be defined as the occurrence of postoperative agitation, confusion, delirium, obtundation, or a transient focal neurological deficit (resolution within 72 h) without any evidence of new structural abnormality on computed tomography or magnetic resonance imaging. Myocardial infarction [41] will be defined as a rise and/or fall of cardiac troponin values at least one value above the 99th percentile upper reference limit and at least one of the following: symptoms of myocardial ischemia, new ischemic electrocardiogram (ECG) changes, development of pathological Q waves, imaging evidence of new loss of viable myocardium or new regional wall motion abnormality in a pattern consistent with an ischemic etiology, or the identification of a coronary thrombus by angiography or autopsy (but not for type 2 or 3 MI). Prolonged intubation will be defined as a requirement of intubation lasting more than 48 h.

Tertiary outcomes include the length of ICU stay, length of hospital stay, length of endotracheal intubation, volume of perioperative blood product transfusions, as well as total hospitalization cost. The proportion of patients who develop postoperative ascites will serve as a measure of safety in this trial.

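### The continuous tertiary outcomes are compared without centre or EuroSCORE II, and the rank test named for non-normal data is a paired test that does not fit two independent arms

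*Protocol article*

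**What the plan says.** The Data analysis section of the protocol article gives one rule, with two options, for all continuous variables. The first option is the *t* test: "differences in such variables will be analyzed using an independent". The second follows directly after it: "test or the Wilcoxon signed-rank test, depending on whether data are normally distributed". The section mentions no centre term and no covariate. The only regression follows later in that section: "Univariate and multivariate logistic regression will be performed to determine relative risk of primary and secondary outcomes". Tertiary outcomes are not included in it.

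The continuous endpoints are tertiary. Under Study outcomes: "Tertiary outcomes include the length of ICU stay, length of hospital stay, length of endotracheal intubation, volume of perioperative blood product transfusions". Hospital cost closes the same list: "as well as total hospitalization cost". The data come from several hospitals (Study design: "Five clinical research centers in China will participate") and from patients "scheduled for elective or emergency TARS under CPB" (Recruitment of study population). The Baseline study visit section lists EuroSCORE II, comorbidities and a full blood count among the data collected before surgery. The Objective and hypothesis section includes shorter ventilation and a shorter ICU stay in what the trial expects to show.

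**The concern.** There are two faults in one sentence.

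The first is a wrong test. The signed-rank test works on within-pair differences or on a single sample. Patients here are assigned individually to one of two parallel arms, so no pairs exist. Lengths of stay, transfusion volumes and costs are usually skewed, so this branch may well be the one used.

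The second is avoidable loss of precision. Stay, extubation, transfusion and cost plausibly differ between hospitals and with preoperative risk; for example, the Study design section keeps patients in the ICU until they are judged stable enough to move, which is a local decision. An unadjusted comparison leaves that variation in the error term. The trial was sized on the binary composite alone, and no power is stated for the continuous outcomes. Two of them carry part of the hypothesis, so a real reduction could be missed that the same data, analysed with recorded baseline information, would show.

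**Working it through.** **The plan's own figure.** Inputs from Sample size calculation: 34.2% versus 23.7%, two-sided 5%, power 80%, dropout 10%.

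- n = (1.960 + 0.842)² × [0.342 × 0.658 + 0.237 × 0.763] / 0.105² = 288.9, so 289 per arm.
- 289 × 1.10 = 317.9, so 318 per arm and 636 in total, as stated.

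This figure concerns the binary composite only. The article gives no standard deviation, between-centre variance or covariate correlation for any continuous outcome, so the rest is conditional on assumed values.

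**Precision for means.** Let R² be the assumed share of outcome variance explained by centre plus baseline risk.

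- Effect detectable without adjustment at 80% power, 318 per arm: (1.960 + 0.842) × √(2/318) = 0.222 SD.
- Adjustment multiplies the standard error by √(1 − R²).
- Adjusted power for 0.222 SD: Φ(2.802/√(1 − R²) − 1.960).
- Adjusted N with the precision of 636 unadjusted: 636 × (1 − R²).

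| Assumed R² | SE ratio | Adjusted power | Equivalent N |
|---|---|---|---|
| 0 | 1.000 | 80% | 636 |
| 0.05 | 0.975 | 82% | 604 |
| 0.10 | 0.949 | 84% | 572 |
| 0.20 | 0.894 | 88% | 509 |
| 0.30 | 0.837 | 92% | 445 |
| 0.50 | 0.707 | 98% | 318 |

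With 286 per arm (10% lost), the detectable effect is 0.234 SD unadjusted, 0.222 SD at R² = 0.10 and 0.196 SD at R² = 0.30.

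**Validity of the *t* test.** Simulation of 636 patients in five centres, 3,000 runs per setting, centre explaining 2%, 10%, 20% or 30% of the variance:

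- Simple 1:1 randomization: type I error of the unadjusted *t* test was 0.042 to 0.058, and its power stayed near 80% for 0.222 SD.
- Randomization stratified by centre: type I error fell to 0.048, 0.042, 0.034 and 0.017, so the unadjusted test became conservative.

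The Randomization and blinding section does not say which of the two applies.

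**Rank tests.** No power can be attached to the signed-rank test here, because the design supplies no pairs. The comparison is therefore between the ordinary rank-sum test and its centre-stratified form. Assumptions: log-normal outcome, 12% shorter stay, within-centre SD 0.5 on the log scale, centre variance added on top, unstratified randomization.

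- No centre differences: about 88% power for both.
- Centre share 20%: pooled rank-sum 79–82%.
- Centre share 50%: pooled rank-sum 58–67%.
- Centre-stratified test: about 86–90% throughout.

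The lower end of each range comes from centre effects scaled to a fixed spread, and the upper end from centre effects drawn at random. The fall in pooled power also reflects that total variance grows with the centre share in this set-up. The useful reading is the gap between the two tests at a given share.

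**The case against.** The strongest reply is that an unadjusted comparison of individually randomized arms is valid, so adjustment is a matter of efficiency. The article condenses a fuller protocol, and covariate adjustment is often left to an analysis plan that is not shown. These outcomes are tertiary and no power is claimed for them. Ventilation is also partly covered, since intubation beyond 48 hours is a secondary outcome and falls under the logistic regression.

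Most of this stands. It limits the point to precision and leaves the primary conclusion untouched. It does not remove the point, because the article states a method for continuous variables and an analysis plan that follows it would inherit both faults. The choice of a paired test is an error on any reading.

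A reader might go further and infer that hospital differences swamp the treatment effect, or that pooling the five centres biases it. The documents support neither. They give no between-centre variance, and at an assumed R² of 0.05 to 0.10 the loss is only 2 to 4 power points. Randomization of individual patients means that centre adds noise, not bias. Nor can it be taken for granted that every useful covariate is already recorded: elective or emergency status describes the target population but is absent from the variables listed for the baseline visit.

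**Conclusion.** The point holds in a limited form. For non-normal continuous outcomes the named test does not fit the design and has to be replaced. For normal outcomes the named *t* test is valid, or conservative if randomization is stratified by centre, but it forgoes precision that recorded centre and EuroSCORE II could recover. The gain is minor if these explain 5–10% of the variance and material from about 20%, where 80% power becomes 88%. Those shares are assumptions, and the true value cannot be obtained from the article. The simulations rest further on the assumed centre sizes, distributions and effect.

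**What to change.** In the Data analysis section, replace the rule for the continuous tertiary outcomes with a prespecified linear model with robust standard errors, containing arm, centre and EuroSCORE II. Add baseline hemoglobin for transfusion volume, and urgency of surgery if it is recorded. Fix the scale for each outcome in advance so that it is not chosen from the data, and keep cost on the original scale if the difference in mean cost is of interest, because a log model estimates a ratio of geometric means. Where a rank test is used, name the centre-stratified (van Elteren) rank-sum test in place of the signed-rank test.

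The cost is one sentence of analysis wording. Centre, EuroSCORE II and the blood count are already available, and no extra patients are needed.

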### Study outcomes

The primary outcome will be a composite of operative mortality and major complications, including paraplegia, postoperative renal failure, severe liver dysfunction, and gastrointestinal complications. Operative mortality is defined as any death that occurs in the same hospital in which the surgery was performed. Other complications will be defined according to the Society of Thoracic Surgery (https://www.sts.org/). The primary outcome will be measured throughout hospitalization (regardless of length of stay) and for up to 30 days after surgery if the patient is discharged. The decision to initiate renal replacement therapy (RRT) will be made by experienced staff in the cardiac ICU. Patients are given RRT if they are classified as grade F according to the RIFLE criteria: serum creatinine ≥ 4 mg/dL or an increase of at least threefold in baseline serum creatinine, or > 75% decline in the estimated glomerular filtration rate. Urine output < 0.3 mL/kg/h for 24 h or anuria for 12 h. We have defined RRT as intermittent hemodialysis or continuous venovenous hemofiltration [38].

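### The test named for non-normal continuous variables, the Wilcoxon signed-rank test, is a paired test and does not fit two independent arms; it is probably a slip for the rank-sum test

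*Protocol article*

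**What the plan says.** The Study design section of the protocol article describes a "multicenter, randomized controlled, assessor-blind, parallel-group study with a superiority framework". Participants "will be randomly assigned by computer to either the MHCA (control) group or the RIVP group at a ratio of 1:1". Neither that section nor any other describes matching, crossover or a within-patient treatment comparison.

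For continuous variables, the Data analysis section says that "differences in such variables will be analyzed using an independent *t* test" or "the Wilcoxon signed-rank test, depending on whether data are normally distributed". The rank-sum or Mann-Whitney test is not named anywhere in the article.

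The continuous outcomes are listed in Study outcomes: "Tertiary outcomes include the length of ICU stay, length of hospital stay, length of endotracheal intubation, volume of perioperative blood product transfusions", and total hospitalization cost. The Objective and hypothesis section includes shorter ventilation and shorter ICU stay among the expected benefits.

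**The concern.** The two branches of the rule do not match. The t test is for independent samples. The test that replaces it when data are not normal is for paired differences, or for one sample against a fixed value. The design supplies no pairs, so an analyst who follows the text must invent them or depart from the published rule.

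Durations, transfusion volumes and costs are often right-skewed. If that holds here, the non-normal branch would govern most tertiary outcomes, including the two durations that the stated hypothesis mentions. The article gives no distribution for any of them, so this is an expectation and not a fact from the document.

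**Working it through.** **1. Does the design supply pairs?** Setting the sections side by side:

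| Section | Content | Implication |
|---|---|---|
| Study design | Individual 1:1 randomization, parallel groups | Two independent samples |
| Data analysis, normal data | Independent t test | Between-arm comparison of independent samples |
| Data analysis, non-normal data | Wilcoxon signed-rank test | Needs paired or one-sample data |
| Study outcomes, tertiary | Stay, intubation time, transfusion volume, cost | No baseline value to pair with |

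The third row conflicts with the other three.

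**2. Which outcomes does the rule reach?** The primary outcome is binary: "The primary outcome will be a composite of operative mortality and major complications". The secondary outcomes are proportions of patients. The Data analysis section sends categorical variables to chi-square and Fisher tests, and adds log-rank and logistic regression for primary and secondary outcomes. None of these uses the signed-rank test.

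**3. Is the sample size touched?** The plan's own formula with its own inputs (34.2% and 23.7%, two-sided 5%, 80% power) gives:

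- n = (1.960 + 0.842)² × [0.342 × 0.658 + 0.237 × 0.763] / 0.105² = 288.9, so 289 per arm.
- Adding 10% for dropout: 289 × 1.10 = 317.9, so 318 per arm and 2 × 318 = 636.

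The stated figure reproduces. It rests on the binary composite alone, so the choice of test for continuous variables does not enter it.

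**4. What happens if the test is run as written?** The article gives no data on continuous outcomes, so the following rests on assumed log-normal values with a log SD of 0.8.

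*Unequal arms.* With 286 and 283 patients analysed, the two-sample call to the signed-rank test fails because the patients cannot be paired. The rank-sum test runs. The plan allows for 10% dropout, so exactly equal arms are unlikely.

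*Equal arms, arbitrary pairing.* Each row is one simulated data set, re-paired at random 1,000 times (2,000 for the last row). The shift is 0.16 on the log scale (exp(−0.16) = 0.85, about 15% shorter) in the first row, about 15% in the next three, and 0.15 on the log scale (exp(−0.15) = 0.86, about 14%) in the last.

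| Per arm | Rank-sum p | Signed-rank p over pairings |
|---|---|---|
| 300 | 0.0031 | 0.0004 to 0.057 (median 0.0076) |
| 300 | 0.009 | 0.0006 to 0.068 |
| 318 | 0.048 | 0.003 to 0.18; 62% below 0.05 |
| 300 | 0.059 | 0.003 to 0.23; 46% below 0.05 |
| 318 | 0.114 | 0.010 to 0.40 (median 0.10) |

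With a clear effect the pairing seldom changes the conclusion: in a data set with the first row's figures, only 2 of 1,000 pairings exceeded 0.05. Near the threshold the pairing decides it.

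*Long-run behaviour.* If pairing is unrelated to outcome and the arms have the same distribution, each paired difference is symmetric about zero. That is what the signed-rank test assumes under the null, so its level should hold. In 3,000 simulated trials of 300 per arm, the type I error was 5.0% for signed-rank and 4.7% for rank-sum. The simulation error is about √(0.05 × 0.95 / 3,000) = 0.4 percentage points, so these do not differ materially. Power at the 15% shift was 63% against 67%.

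**The case against.** The strongest reply is that nobody will do this. The test stands beside an independent t test as its non-normal counterpart, so the rank-sum test is clearly meant, and a competent statistician would use it without comment. This stands as a reading of intent and lowers the severity. It does not correct the text: the article fixes a specific test, and nothing else in it supplies the right one.

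A second reply is that the signed-rank test might be meant for changes within patients, since baseline and daily postoperative values are collected. The wording does not allow this. Normality alone decides between the two tests, so both must answer the same between-arm question.

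A reader might infer more than the document supports. One inference is that the error inflates false positives or systematically distorts results. With random pairing it does not: the level holds and about 4 points of power are lost. Sorting the file by outcome would invalidate the test, but the plan does not call for that. Another inference is that the trial's main conclusion is at risk. It is not, because the primary and secondary outcomes are binary. Nor does the wide range of p-values mean that most conclusions would flip; that happens mainly near the threshold.

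**Conclusion.** The named test is wrong for this design. The reading that the document supports is a probable naming slip, confined to continuous variables judged non-normal and mainly the tertiary outcomes. Ventilation time and ICU stay give it some weight because they appear in the stated hypothesis, although Study outcomes ranks both durations as tertiary.

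Taken literally, the rule either cannot be carried out with unequal arms or yields a p-value that depends on an arbitrary order of patients, with slightly lower power. The design conflict follows from the document alone. The sizes rest on the assumed log-normal model, log SD and effect, and illustrate the behaviour without predicting this trial's data. The binary primary and secondary outcomes and the 636 patients are unaffected. Severity: minor to moderate.

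**What to change.** In the Data analysis section, replace 'Wilcoxon signed-rank test' with 'Wilcoxon rank-sum (Mann-Whitney U) test'. If a separate analysis plan repeats the wording, correct it there too, before the allocation is revealed. This is a change of wording only: it does not affect sample size, data collection or conduct. A Hodges-Lehmann difference with a 95% confidence interval could be reported beside the test, but that is optional and the correction does not depend on it.

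### The normality rule would send total hospitalization cost to a rank test and probably a median, and neither estimates the difference in mean cost needed to state a saving

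*Protocol article*

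**What the plan says.** In the protocol article, the Study outcomes section lists among the tertiary outcomes "volume of perioperative blood product transfusions, as well as total hospitalization cost".

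The Data analysis section handles all continuous variables together. On summaries it says "Continuous variables will be expressed as mean ± standard deviation or median (interquartile range". On tests it offers an independent-groups t test or Wilcoxon's signed-rank test, the choice "depending on whether data are normally distributed". Cost is not exempted from this rule, and no comparison of mean cost is planned for the case where the data are not normal.

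The Objective and hypothesis section does not mention cost. Its hypotheses concern mortality, major complications, temporary neurological defects, ventilation time and ICU stay.

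**The concern.** Hospital cost is usually right-skewed. With about 300 patients per arm, almost any normality check will detect this, so the stated rule points cost to the rank branch. A rank test compares how the two distributions are ordered, and a median describes the typical patient. A saving is a difference in arithmetic means, because the mean times the number of patients is the bill. Neither a rank p-value nor a median difference can be converted into that figure.

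The two approaches diverge most when a treatment removes a few very expensive courses and adds a little to everyone's cost. RIVP could fit that description. Its rationale is fewer major complications in a minority of patients, and it adds a re-routed line and an extra sucker in every treated patient (Experimental intervention protocol). The document puts no cost on these additions.

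**Working it through.** **The plan's own figure.** The only number the article computes is the sample size. With p1 = 0.342 (13/38) and p2 = 0.237 (9/38), two-sided 5% and 80% power:

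n = (1.960 + 0.842)² × [0.342×0.658 + 0.237×0.763] / 0.105² ≈ 7.85 × 0.406 / 0.011025 ≈ 289 per arm.

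Multiplying by 1.1 for 10% dropout gives 318 per arm, 636 in total, as stated. This figure rests on the primary composite and does not involve cost.

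**Which branch cost would take.** The article gives no cost data, so skewness is an assumption. In simulated data with 318 per arm, log-normal base cost (coefficient of variation 0.35) and complicated patients costing only twice as much, a Shapiro-Wilk test rejected normality in essentially all of 500 samples.

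**Cost model (assumed).** Base cost is log-normal with mean 1 and coefficient of variation 0.35. A patient with a composite event costs k times as much. RIVP adds a fixed amount a, as a fraction of base cost, to every patient. Event rates are the pilot's 34.2% and 23.7%, with 318 per arm. Only these rates and the arm size come from the article; k and a are assumptions.

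Mean saving = 0.105 × (k − 1) − a.

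| k | a | mean saving (base cost = 1) | power, ranks (Mann-Whitney) | power, means (Welch) |
|---|---|---|---|---|
| 2 | 0 | 0.105 | 50% | 51% |
| 3 | 0 | 0.210 | 60% | 66% |
| 4 | 0 | 0.315 | 62% | 71% |
| 4 | 0.05 | 0.265 | 26% | 58% |
| 3 | 0.10 | 0.110 | 5% | 26% |
| 4 | 0.10 | 0.215 | 5% | 40% |

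**Hand check of the last row, means column.**
- Mean cost: control 1 + 0.342×3 = 2.026; RIVP 1 + 0.237×3 + 0.10 = 1.811; difference 0.215.
- Variance, control: 1.1225 × (0.658 + 0.342×16) − 2.026² = 2.776.
- Variance, RIVP: 1.1225 × (0.763 + 0.237×16) − 1.711² = 2.186 (the fixed addition does not change it).
- Standard error: √[(2.776 + 2.186)/318] = 0.125.
- Power: Φ(0.215/0.125 − 1.96) = Φ(−0.24) ≈ 0.41, in line with the simulated 40%.

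**Direction.** At k = 4 and a = 0.10 the median also falls under RIVP, by about 0.02, so mean and median agree in sign. At k = 2 and a = 0.10 the median rises by about 0.015, but the mean saving is only 0.105 − 0.10 = 0.005, which is practically nil.

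**A second cost model.** With 286 per arm (318 × 0.9), log-SD 0.3, the pilot rates and no added cost, power is 0.58 for ranks at both three and five times cost, against 0.67 and 0.72 for means. Larger gaps appear if the expensive group is small. If it falls from 10% to 5% at five times cost, power is 0.18 against 0.54. If it falls from 10% to 3% with typical RIVP cost 5% higher, power is 0.05 against 0.70 and the median is 2% higher under RIVP although mean cost falls by 16%. Those shares are not in the document.

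**The case against.** The strongest reply is that this is analysis-plan detail. A journal article gave a default for continuous variables, and the estimator for one tertiary outcome is commonly left to a fuller document. That would dispose of a complaint about something missing. Here, though, the article states a rule, the rule covers cost, and it suits cost poorly. It is fair to add that the normality clause attaches most directly to the choice of test; that it also decides between mean and median is a likely reading, not an explicit one. Nor does the rule forbid reporting mean cost as well.

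The article also states no economic hypothesis, so no declared claim of a saving is put at risk. This stands and keeps the point small.

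The cost model is simple. The composite includes deaths (4 and 3 in the pilot), and an early death may lower cost. Postoperative renal failure differed by one patient (7 against 6). The documents therefore do not show that the full 34.2% to 23.7% contrast translates into avoided expense. This also stands, and it is why the power figures are illustrations only.

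A reader might infer that the trial is likely to miss a real saving, or to report RIVP as dearer when mean cost truly falls. The documents do not support either. The large power losses at the pilot rates need an added per-patient cost that the article never gives. In the scenarios examined at those rates, with up to 10% added, the only reversal comes with a mean difference of almost zero. A reversal alongside a real saving appeared only with event shares found nowhere in the article.

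**Conclusion.** The point holds as a minor one about what is estimated. Under the stated rule, cost would very likely be compared on ranks and probably described by a median, and neither gives the mean difference. That conclusion rests on cost being skewed, which the document does not show but which is a safe expectation.

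The effect on power is conditional. It ranges from negligible to modest at the pilot rates if RIVP adds no cost per patient, and is substantial only if it adds about 5–10% of base cost. Cost is tertiary, so neither the primary conclusion nor the sample size of 636 changes.

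One plain error sits in the same sentence: the signed-rank test is for paired observations, while the two arms are independent. Correcting the name alone would not resolve the cost question.

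**What to change.** In Data analysis, add that total hospitalization cost will be compared as the difference in arithmetic means between arms with a bootstrap 95% confidence interval, whatever the normality check shows, and that median and interquartile range are descriptive only. For other non-normal continuous variables, replace the signed-rank test with the rank-sum (Mann-Whitney) test for independent groups.

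This takes two sentences, settled before unblinding, and needs no extra data, patients or change in sample size. The downside is a wider interval for mean cost if a few patients are extreme, which reflects real uncertainty about the bill.
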